### Electroencephalography (EEG) recording

The EEG recording procedure will include rest, listening to the TIMP music patterns (that will be learned in the sessions) a Go/No go task, after which another resting state EEG will be recorded. This study will utilize a BrainAmp DC (Brainproducts) EEG utilizing 64 active electrodes and artifact channels (EOG, EMG). Artifact control will be guided by video recording of the participant whilst undergoing EEG. The video footage will inform about body movement and eye-blinks. After visual inspection and indexing of the continuous EEG traces, data pre-processing will utilize the Neuroguide Artifact toolbox (Thatcher et al., 2009) for the resting EEG and the music listening task. EEGLAB and ePrime will be used for the analysis of the Go/No Go task and will focus on the short episodes around the clicks. After visual inspection ICA will be applied to pre-process data and determined artifacts will be excluded.

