## EEG analysis

EEG case analysis of the pre/post *resting state* EEG recordings will be treated with NeuroGuide Software (www.appliedneuroscience.com; Version 2.6.6) including an age, gender and condition-matched (*N* = 678 matched controls) LORETA normative EEG database (Thatcher et al., 2005). Continuous, artifact-free, raw EEG data will be subjected to a power spectral analysis (PSA) to calculate raw and z-scored spectral values, topography (Absolute power and Current Source Density), electrode correlation, burst metrics (burst number, amplitude, duration, and interval), instantaneous connectivity and coherence patterns, especially beta coherence. Due to the small sample size (*N* = 2) we do not expect significant differences between subjects' resting state displayed on central and temporal leads in beta power *z*-score topography and coherence data in the early compared to delayed intervention. However, we do expect intra-subject pre/post intervention z-score decreases in temporal and central leads. Topography will explore post-therapy spectral power in-, or decreases in central and temporal areas; coherence data of central and temporal leads will inform about post-therapy connectivity decreases or increases between motor and auditory cortex (as seen in beta coherence; Altenmüller et al., 2009). Pre/post intervention paired *t*-test will indicate the probabilities and directions of change. We expect the post-intervention measures to show a lowering of *z*-scores, i.e., normalization, and an increase of brain connectivity between central and temporal regions.

Low Resolution Tomography (LORETA), a specific mathematical solution to EEG source localization (Pascual-Marqui et al., 1994), will inform about raw and z-transformed current density means and their pre/post differences (subtraction/individual paired *t*-test) especially of the beta range. Further raw and z-transformed Region of Interest (ROI) correlations of primary and pre-motor [Brodmann Area (BA) 4,6, Pre central gyrus], auditory (BA 22, 41, 42, superior and transversal temporal gryus) and frontal (BA 44, 45, inferior frontal gyrus) cortices will inform about post-treatment related neural reorganization in audio-motor coupling, expected to be shown as increased ROI correlations.

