A previous study observed post therapy changes in motor and auditory activity during the music listening (Altenmüller et al., 2009; Rojo et al., 2011). In this study we will compare the pre/post *music listening data* of TIMP patterns employed in the intervention. In Rojo's study, when the participant listened to the music played in sessions after the MST treatment period, they displayed an increase of motor and auditory responses when compared to listening before they had received any MST. We hope to demonstrate the same tendencies by utilizing topographic EEG mapping and LORETA. Differences in power means and probabilities of change will inform us about differences in responses to the particular TIMP patterns.

We will analyse the particular raw pre/post means and differences of listening sequences (see Table 1) on topography shifts (Absolute power and CSD), electrode correlation (PCC), burst metrics, instantaneous connectivity, phase and coherence patterns in particular on the beta range (Altenmüller et al., 2009). Altenmüller further investigated alpha ERD/S measured after hitting a trigger pad and was able to show differences in the response latencies. Increases in frontal midline theta (FMT) triggered by emotional responses during music listening have been reported in several music therapy studies (Sammler et al., 2007; Lee et al., 2012; Fachner et al., 2013; O'Kelly et al., 2013). We expect to see more increases in FMT post TIMP treatment (6 weeks). We will apply LORETA ROI correlation of beta, alpha and theta frequency power means for each TIMP pattern (see Table 1) to indicate task related pre-post changes in auditory, frontal and motor regions (see rest EEG analysis).

**Table 1 T1:** **TIMP chart**.

	**Target movement (bold) and associated muscle groups**	**Instrument/s and equipment**	**Positioning**	**Participant instructions**	**Playing pattern**	**Facilitating music**	**Variations**

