ARAT and 9HPT data will not inform about treatment effects on audio-motor coupling and neural re-organization as demonstrated in other studies with fMRI, TMS, and EEG (Altenmüller et al., 2009; Rojo et al., 2011; Rodriguez-fornells et al., 2012). In order to estimate the feasibility of neurometric EEG measures (John, 1989) as an imaging tool for determining cerebral changes related to the TIMP intervention we plan to visualize audio-motor coupling (Rodriguez-fornells et al., 2012) with the continuous EEG using one participant from each group. A mathematical solution of the inverse problem of EEG sources allows the creation of a low resolution electromagnetic tomography (LORETA) of brain regions (Pascual-Marqui et al., 1994) and we can correlate the estimated EEG source activity of the raw and *z*-scored transformed means (Thatcher et al., 2005). EEG cannot visualize brain activity of the midbrain but of the cortex and this is where we expect most lesions after stroke.

Utilizing these imaging tools we also plan to explore a comparison of differences between early and late intervention. Two clients will be subjected to an EEG but we are aware that the imaging results will not be as high resolution as those provided by fMRI. Furthermore, with only two participants, no resulting statistical differences are sought or expected. EEG measures changes in electrical current in the brain and has been utilized in studies on the recovery of stroke patients (Giaquinto et al., 1994), prefrontal-to-motor cortex connectivity (Picazio et al., 2014), post-movement beta-event-related-synchronization (PMBS) in stroke patients with mild hemiparesis (Eder et al., 2006) and current stroke studies utilizing MST in stroke rehabilitation (Altenmüller et al., 2009; Rodriguez-fornells et al., 2012). To explore the limitations and advances of the imaging techniques proposed for this study, the manageability of the measurement process and the cost-effectiveness of utilizing low-cost, portable EEG apparatus and analysis, compared to lab-based, more expensive fMRI measures is a legitimate goal for a feasibility study.

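### Pre/post paired t-tests within single EEG participants cannot give probabilities of treatment-related change, because each person has only one occasion before and one after TIMP

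*Protocol article*

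**What the plan says.** The Discussion section of the protocol article plans to visualise audio-motor coupling "with the continuous EEG using one participant from each group", so there are two EEG participants in all.

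The EEG analysis section sets out what is done with their recordings:

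- Between the two people, it says that "we do not expect significant differences between subjects' resting state displayed on central and temporal leads" in the early compared with the delayed intervention, and gives the small sample as the reason.
- Within each person, it continues: "However, we do expect intra-subject pre/post intervention z-score decreases in temporal and central leads".
- For the resting-state data, a pre/post paired t-test "will indicate the probabilities and directions of change".
- For LORETA current density, the pre/post differences are to be examined by "subtraction/individual paired *t*-test) especially of the beta range".
- For the music-listening data, the same section says: "Differences in power means and probabilities of change will inform us about differences in responses to the particular TIMP patterns". No test is named there.

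The Discussion later states that "with only two participants, no resulting statistical differences are sought or expected". The article does not name the unit of replication for any of the t-tests.

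**The concern.** A paired t-test needs several pairs that vary independently of one another. A pre/post comparison in one person supplies one pair. The words used (individual, intra-subject) place the test inside the person, so the replicates can only be parts of the two recordings: epochs, leads, frequency bins or voxels. All parts of a recording share that session's electrode placement and the participant's state at the time. The spread among them does not measure how much a person's EEG differs between two sessions for reasons unrelated to treatment.

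What is at stake is how the EEG results are read. The section states the expected direction in advance: lower z-scores, described as normalisation. An ordinary difference between sessions in that direction, carrying a small P-value, could be taken as confirmation. The Discussion says that ARAT and 9HPT cannot inform on neural reorganisation, so neither can correct such a reading.

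**Working it through.** The article gives no sample size, power or error-rate figure for the EEG component, so there is no stated figure to reproduce. The check has three steps, all at an assumed two-sided 5% level.

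**1. Person as unit**

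Inputs from the article: two participants, each compared once before and once after TIMP.

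- Within one person: 1 difference, df = 1 − 1 = 0. The standard error cannot be estimated and no t-test exists.
- Across both people: 2 differences, df = 2 − 1 = 1. The critical |t| is 12.71. Power from the noncentral t is about 9% for a standardised mean change of 1 and about 18% for a change of 2.

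**2. Segments of the recording as unit, with an ordinary session-to-session shift**

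Assumed inputs, none of them in the article: m segments per session, independent within a session with SD σ; each session has its own random level with SD τ; the treatment effect is zero.

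- True variance of the pre/post mean difference: 2τ² + 2σ²/m.
- Variance that the t-test estimates: 2σ²/m.
- Ratio: R = 1 + m(τ/σ)².
- Type I error ≈ 2[1 − Φ(t_crit/√R)]. With m = 60, t_crit is about 2.00 (59 df).

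| τ/σ | Session share of total variance | R | Type I error |
|---|---|---|---|
| 0.2 | 0.04/1.04 = 4% | 1 + 60 × 0.04 = 3.4 | 28% |
| 0.3 | 0.09/1.09 = 8% | 1 + 60 × 0.09 = 6.4 | 43% |
| 0.5 | 0.25/1.25 = 20% | 1 + 60 × 0.25 = 16.0 | 62% |

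The same model, written in terms of the session's share of total variance (s) and evaluated exactly from t = √(1 + m·s/(1 − s)) × t(m−1), shows the effect of recording length. At a share of 10%, the error is 33% with 30 segments, 47% with 60 and 60% with 120. In this model more segments make the error worse.

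**3. Segments as unit, with no session shift but serial correlation**

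Assumed inputs: first-order autoregressive segments, 60 or 120 per session, 20,000 simulated data sets. The type I error is about 15%, 25% and 42% at lag-1 correlations of 0.3, 0.5 and 0.7. With zero correlation it is 5%, as it should be.

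Under these models the nominal level is kept only if segments are independent and sessions never differ by chance.

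**The two statements on significance, side by side**

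The EEG analysis section disclaims significance between subjects and then turns, with a contrast word, to within-subject change and to the t-tests. The Discussion's disclaimer is unqualified in its wording, but it stands in a paragraph that opens with the comparison of early and late intervention.

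**The case against.** The strongest reply is that this is an exploratory, two-case part of a feasibility study. The Discussion gives its purpose as testing the feasibility, manageability and cost of EEG as a tool. The t-test is one item beside normative z-scores, topography, coherence and region-of-interest correlations, and plain subtraction is already listed with it for LORETA. The phrase about treatment-related neural reorganisation is attached to the region-of-interest correlations, not to the t-tests. The unit of analysis is detail that an article may leave to a fuller document, and the listening data do have a natural pairing, because the same TIMP patterns are heard before and after.

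Much of this stands, and it limits the point. It does not rescue the test. Whichever unit a fuller document names, there is still one session on each side of treatment, and pairing by pattern does not remove what is common to a session. Exploration justifies description, but it does not make the P-value a probability of treatment-related change.

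Three stronger readings are tempting and are not supported:

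- *That the Discussion flatly contradicts the EEG analysis section.* Its context, and the between/within split in the EEG analysis section, allow it to be read as covering only early versus late. It is a wording conflict to reconcile.
- *That this plan's error rate is 28% to 62%.* Those figures rest wholly on assumed inputs and apply only if segments are the unit. They also show that a small session shift often does not produce significance: at τ/σ = 0.2, 72% of tests do not reject.
- *That the EEG P-values are the study's imaging conclusion.* The article does not say so.

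**Conclusion.** The concern holds for the within-person P-values. The EEG analysis section names a test, places it within the individual and reads its result as a probability of change. The design cannot supply that probability: there are 0 degrees of freedom within a person and 1 across both. P-values built from parts of two recordings can at best show that two sessions differ, and serial or spatial correlation may distort them further. This conclusion rests on the article's pre/post design and two participants, and not on the illustrative error rates.

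The size of the inflation in this trial is unknown, because the article gives no segment count, session variance or correlation. For the listening data the point is narrower: probabilities are to be interpreted there, but no t-test is named. The consequence is limited to the exploratory EEG component, and the primary ARAT analysis is unaffected.

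**What to change.** 1. In the EEG analysis section, delete the paired t-tests for the resting-state and LORETA data, and remove probabilities of change from both the resting-state and the music-listening text.
2. Report each participant's pre value, post value and difference descriptively, without P-values, and state that these differences cannot be separated from session-to-session variation.
3. Reword the Discussion so that it is clear whether its disclaimer on statistical differences covers only early versus late intervention or all EEG comparisons.

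It may be tempting to judge the pre/post change against the difference between the two resting recordings in a session, since the Electroencephalography (EEG) recording section describes an opening rest, then music listening and a Go/No go task, "after which another resting state EEG will be recorded". This should not be used as a yardstick. Both rests belong to one session, so their difference cannot show variation between sessions, and it may also reflect fatigue or carry-over from the tasks between them.

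The cost is a few sentences of rewording and slightly less analysis. The EEG report loses its P-values. Data collection and the feasibility aim for EEG are unchanged.

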12	**Wrist and forearm pronation and supination,** shoulder adduction, elbow extension, core muscles	**Cymbal on boom and bongos on stand,** two drum sticks or beaters taped together so there is a tip at either end or single stick/beater rotated so that tip plays cymbal then bongo	Cymbal and bongos slightly less than a beater's distance apart focusing efforts on wrist and forearm rotation Alternatively, play bongos, rotating wrist/forearm to play bongo 1 then bongo 2	Sung prompt: turn and turn and play	Affected hand only plays bongo with one end of the stick, then cymbal or bongo 2 with the other end on beat 3 only (slow rotation) or 1 and 3	Octaves or chords: F slide to C, slide to Gm, slide to Dm 4/4 time over 2 bars, with strong accent on beats 1 and 3 and crescendo between each chord	**A:** holding just the adaptive beater and making full forearm pronation and supination movement to play cymbal then bongo or bongo 1, bongo 2 **B:** using a cabasa instead of stick/beater

*Patterns gradually increase in complexity; 1–5, gross motor; 6–10, fine motor; 11 and 12, grip and release, pronation and supination*.

A Go/No Go *task* will be performed to track improvements in reaction time (measuring participant's response to visual stimuli with a button press) and changes in contingent negative variation (CNV) between signals as a marker of attention processes. We expect the reaction time to have shortened more in the early intervention group.

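### With one EEG participant per arm, the predicted early-treatment advantage in reaction time cannot be assessed, pre/post P-values cannot show treatment-related reorganisation, and normalisation is given the wrong sign for negative z-scores

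*Protocol article*

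**What the plan says.** - **Sample.** The Discussion plans the EEG "with the continuous EEG using one participant from each group" and repeats that "Two clients will be subjected to an EEG". The EEG analysis section likewise gives N = 2.
- **Go/No Go.** The recording section lists, within the EEG session, "listening to the TIMP music patterns (that will be learned in the sessions) a Go/No go task". Reaction time is therefore also measured in two people.
- **Early versus late.** After Table 1 the EEG analysis section states: "We expect the reaction time to have shortened more in the early intervention group". For resting EEG the same section expects no significant between-subject difference, because of the small N. The Discussion says that "with only two participants, no resulting statistical differences are sought or expected".
- **Pre/post.** The EEG analysis section expects z-scores to fall within each subject and says that a paired t-test "will indicate the probabilities and directions of change". For LORETA it calls the paired t-test individual, and it says that region-of-interest correlations will inform about reorganisation related to treatment. The music-listening paragraph also relies on probabilities of change.
- **Normalisation.** A fall in z-scores after treatment is glossed as "i.e., normalization, and an increase of brain connectivity between central and temporal regions".

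**The concern.** Three stated items do not fit a two-case design.

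1. A prediction about a group is made where each group is one person. Eligibility runs from 3 to 60 months post stroke and from age 18 to 90, and the Sample size section stresses heterogeneity of impairment. Any difference between two such people has many explanations other than a nine-week difference in start.
2. Probabilities are to be attached to pre/post change and read as information about the effect of treatment. Each person has one recording before and one after, so ordinary variation between two sessions cannot be separated from change due to TIMP.
3. The definition of improvement has a fixed sign although the target, a z of zero, can be approached from either side.

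At stake is the reading of the EEG cases: session-to-session noise could be taken for reorganisation, a difference between two people for a benefit of early treatment, and a move away from the norm for recovery.

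**Working it through.** The article gives no power, alpha or effect size for the EEG sub-study, so the only figure to reproduce is the count: 1 + 1 = 2, which agrees between the EEG analysis section and the Discussion. A two-sided 5% level is assumed below.

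**Early versus late, 1 versus 1**
- Between-group degrees of freedom: n1 + n2 − 2 = 1 + 1 − 2 = 0. No variance estimate, t-test or confidence interval exists.
- Exact permutation: 2 possible assignments, so the smallest P is 1/2 = 0.50 one-sided and 1.00 two-sided.
- Chance of seeing the predicted direction when the true difference is d standard deviations of change: Φ(d/√2). This gives 0.50 at d = 0, 0.56 at d = 0.2, 0.64 at d = 0.5 and 0.76 at d = 1.0. Seeing the predicted direction says little.

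**Individual pre/post t-test over epochs**
- Let m be the number of epochs per recording and r the ratio of session variance to epoch variance. The article gives neither, so both are assumptions.
- With no treatment effect, the variance of the difference in means is 2(r + 1/m) in units of epoch variance. The t-test estimates it as 2/m. The ratio is 1 + rm.
- False-positive rate ≈ 2Φ(−1.96/√(1 + rm)):

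| r | m | 1 + rm | 1.96/√(1 + rm) | False-positive rate |
|---|---|---|---|---|
| 0.02 | 30 | 1.6 | 1.55 | 12% |
| 0.05 | 60 | 4 | 0.98 | 33% |
| 0.10 | 60 | 7 | 0.74 | 46% |
| 0.20 | 120 | 25 | 0.39 | 70% |

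- A simulation with 20,000 replicates per setting, which sets session variance as a share of total variance, shows the same pattern: about 5% at a share of zero; for shares of 5% to 20%, 21% to 48% with 30 epochs and 47% to 72% with 120.
- More epochs make the problem worse, because they shrink the estimated error but not the session term. Both calculations treat epochs within a recording as independent; positive correlation between them would raise the rates further.

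**Sign of z**
- From +3 to +2, signed z falls by 1 and |z| falls by 1: nearer the norm.
- From −2 to −3, signed z falls by 1 and |z| rises by 1: further from the norm.
- Since z = (value − norm mean)/norm SD, a rise in coherence raises its signed z. Coherence is among the measures listed for raw and z-scored analysis, so a general fall in z and a rise in connectivity pull in opposite directions if both are read on signed coherence z.

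**The case against.** Several stronger readings are tempting, and the document does not support them.

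- **That the plan tests early against late.** It names no such test. It states a direction for reaction time, disclaims significance for resting EEG and otherwise speaks of exploring a comparison. What stands is that the reaction-time expectation carries no such caution and cannot be assessed as a timing effect.
- **That the pre/post test runs across two people.** That would have 1 degree of freedom and a critical t of 12.71, but the text describes intra-subject and individual tests.
- **That the t-tests are invalid outright.** An individual test is computable and can describe a difference between two recordings. What it cannot do is attribute that difference to TIMP.
- **That the Discussion's disclaimer flatly contradicts the t-tests.** It shortly follows the early-versus-late comparison, gives two participants as its reason and may concern differences between participants only. On that reading it sits badly with the reaction-time expectation but not squarely with the individual tests.
- **That the tests carry a multiplicity burden of 64 × 63/2 = 2,016 electrode pairs.** The section directs interpretation to central and temporal leads, beta coherence and named regions. Handling of multiplicity may also sit in a fuller document.

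It is also fair to say that the word normalisation signals an intended move towards the norm, that the section elsewhere allows for change in either direction, and that no rule explicitly scores a move from −2 to −3 as success. The sign problem is thus a faulty stated definition, not proof of a wrong result. The EEG work is an exploratory feasibility exercise, so the consequence is limited.

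**Conclusion.** The point holds in this limited form. The 1-versus-1 result rests only on the document's own count: confounding of person with timing is complete, there are 0 between-group degrees of freedom, and the predicted direction is a coin toss under no effect. The expectation conflicts with the cautions about N = 2 in the EEG analysis section and the Discussion. That P-values from one pre and one post recording cannot support treatment-related reorganisation follows from the design. The size of the inflation, roughly 12–70%, depends on the assumed session variance (2–20% of epoch variance) and epoch count (30–120), and is illustrative. The z-score definition is right only for positive starting values. These are statements to correct in an exploratory sub-study. They do not touch the ARAT primary outcome and do not undermine the trial.

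**What to change.** 1. Delete the expectation of a larger reaction-time gain with early treatment, or reword it as a description of each case.
2. Report each participant's pre/post EEG and reaction-time changes descriptively. Drop the t-test probabilities, or state their unit of replication and label them non-inferential, in both the resting-state and music-listening paragraphs.
3. Define normalisation as a fall in |z|, and state the connectivity expectation on raw coherence.
4. Align the resting-state, music-listening and Go/No Go text with the Discussion, and say there whether its disclaimer covers within-person as well as between-person differences.

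The two resting recordings made within each session should not serve as the noise yardstick for pre/post change. They contain no between-session variance, and the second follows the listening and Go/No Go tasks. At most they can be shown as a lower bound on noise.

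The cost is wording only, with no new data. The loss is that the EEG cases yield no inferential P-values.
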